### Statistical analysis

3.12

After the data for the entire sample has been collected, it will be performed using SPSS 25.0 software package. Missing data will be forecasted and filled using multiple imputations. A logistic regression model will be used to adjust for multiple potential confounders plain. Measurement data obeying the normal distribution will be expressed as mean (standard deviation), and t‐test will be used for comparing between two groups. Non‐normally distributed variables will be expressed as median (interquartile range), and compared by the use of non‐parametric Wilcoxon–Mann–Whitney test. Classification data will be described as cases count (construct Proportional) and compared using the chi‐square test or non‐parametric Wilcoxon–Mann–Whitney test. The confidence interval will be set at 95%. *p* < 0.05 will be considered statistically significant.

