### Sample size calculation

3.4

We estimated the sample size by the use of PASS 15. According to a previous study (Kim & Bang, 2018), the average time of achieving total enteral nutrition in the intervention group and control group is 28.3 days and 33.5 days respectively. This study is a superiority test of two independent means, desired power was set at 0.9, *α* was set at 0.025, *Zα* = 1.64, *Zβ* = 0.84. *σ* represents the standard deviation, and δ represents the difference between the mean values of each group. After calculation, 41 participants were needed for each group. Considering a 20% loss rate, 52 participants were needed for each group. A total of 104 participants should be included.

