### Randomization and blinding

3.6

A third‐party personnel created a randomization schedule which was stratified by birth weight (1000–1499 g and 1500–2000 g) using a computer, and then provided it in sealed, opaque, consecutively numbered envelopes. Participants were assigned randomly to one of the two groups by opening the next envelope sequentially from the appropriate set. An independent research assistant responsible for randomization would inform the massager to perform massage when a neonate was assigned to the massage group, and he is the only person aware of which group the neonate had been assigned to. The massager also knows the list of massage groups. Both of them have no access to data of participants and are not responsible for statistical analysis. A researcher who has no access to the allocation group will perform all the assessments for our study.

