#### Primary outcome

3.10.1

The time (day) from initiation of enteral nutrition to total enteral nutrition, which is defined as a daily intake of ≥120 mL/Kg/day (Abdallah et al., 2013).

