#### Secondary outcome

3.10.2

Days of vomiting, gastric retention (measured by aspirating with a 5‐mL syringe before each feeding) and abdominal distension (defined as a 24‐h abdominal circumference increase of ≥1.5 cm).Weight gain (kg), change of length and head circumference during hospitalization.Length of hospital stay (day).Change of abdomen circumference, gastric retention volume and frequency of defecation (comparison between day 1 and day 7).

Disappearing of vomiting, abdominal distention gastric retention and the amount of milk increased day by day are seemed as alleviation of FI (Lu & Lan, 2020).

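### The only adjusted model named is logistic regression, which does not suit an outcome in days, and the named tests leave out the birth-weight strata used to randomise

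*Protocol article*

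**What the plan says.** Section 3.10.1 defines the primary outcome as "The time (day) from initiation of enteral nutrition to total enteral nutrition". The secondary outcomes in section 3.10.2 are numbers of days, changes in weight, length or circumference, a residual volume and a frequency of defecation. None is defined as yes or no.

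Section 3.12 gives one sentence on adjustment: "A logistic regression model will be used to adjust for multiple potential confounders". It names neither the outcome of that model nor the covariates. For normally distributed measurements it says that a t-"test will be used for comparing between two groups". Non-normal measurements go to the Wilcoxon–Mann–Whitney test, and categorical data to the chi-square or a rank test.

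Section 3.6 describes a "randomization schedule which was stratified by birth weight", with strata of 1000–1499 g and 1500–2000 g; section 3.2 says the same. The strata are not mentioned again in the sample-size section (3.4) or the analysis section (3.12).

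**The concern.** Two things do not fit together.

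First, the adjusted model does not match the outcomes. An ordinary logistic model needs a binary response. The article lists none and gives no cut-point that would make one from days. A reader who wants the adjusted treatment effect on the primary outcome cannot tell from section 3.12 how it will be obtained.

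Second, the design uses birth weight and the analysis does not. Investigators stratify by a factor because they expect it to predict outcome. If it does, leaving it out of the analysis keeps its variance in the residual. Birth weight might be among the unnamed confounders, but it would then sit in a model that does not suit the primary outcome.

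At stake is precision in a trial of 104 infants, and clarity about which adjusted result will be reported.

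**Working it through.** **The plan's own figure.** Section 3.4 gives 41 per group and a 20% loss: 41/(1 − 0.20) = 51.25, rounded up to 52, and 2 × 52 = 104. This step reproduces. The 41 cannot be checked because no SD is stated.

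**Inputs.**
- Difference: the mean time to full feeds "is 28.3 days and 33.5 days respectively" for intervention and control, so δ = 33.5 − 28.3 = 5.2 days.
- Analysed infants: 2 × 41 = 82. Two-sided 5% level (section 3.12).
- SD, back-calculated from SD = δ√(41/2)/(Zα + Zβ). The printed Z values give 5.2 × 4.528/(1.64 + 0.84) = 9.49. The stated α of 0.025, read as one-sided, with power 0.9 gives 5.2 × 4.528/(1.960 + 1.282) = 7.26. The two readings of section 3.4 disagree, so both are used.
- Assumption, not in the article: two equal strata whose means differ by D = 6 to 10 days.

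**Share of variance due to stratum.** R² = D²/(4·SD²), and the residual SD is √(SD² − D²/4).
- SD 9.49: R² = 36/360.2 = 0.10 and 100/360.2 = 0.28; residual SD 9.00 and 8.07.
- SD 7.26: R² = 36/210.8 = 0.17 and 100/210.8 = 0.47; residual SD 6.61 and 5.26.

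**Power.** The ratio δ/(SD·√(2/41)) is compared with the t critical value of 1.99. The unadjusted row uses the total SD, the adjusted rows the residual SD.

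| Analysis | SD 9.49: ratio, power | SD 7.26: ratio, power |
|---|---|---|
| Unadjusted | 2.48, 69% | 3.24, 89% |
| Stratum in model, D = 6 | 2.62, 73% | 3.56, 94% |
| Stratum in model, D = 10 | 2.92, 82% | 4.47, 99% |

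The unadjusted row describes simple allocation within strata. If arms are exactly balanced within strata, the true standard error shrinks by √(1 − R²), while the test still uses the larger one. Unadjusted power is then Φ((ratio − 1.99)/√(1 − R²)). At SD 9.49 this is Φ(0.49/0.949) = 70% and Φ(0.49/0.850) = 72%, still below the adjusted 73% and 82%.

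A simulation of 82 infants gave about 66–68% unadjusted against 71–82% adjusted at SD 9.49, and 89–93% against 93–99% at SD 7.26. It agrees with the table to within a few points.

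**Type I error of the unadjusted test.** With exact balance within strata it is 2(1 − Φ(1.96/√(1 − R²))). At SD 9.49 this is 3.9% for D = 6 and 2.1% for D = 10. Simulation with near-balance gave 4.0% and 2.6%. With simple randomisation within strata it gave 5.0% and 4.7%, so there was no material conservatism. Section 3.6 does not mention blocks, so which case applies is not known from the article.

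**The case against.** The strongest reply is that the primary comparison is sound. Days to full feeds is measurement data, so section 3.12 sends it to the t-test or the rank test, and neither depends on the logistic sentence. This stands. A reader might infer that the primary outcome will be split at a cut-point and that the trial loses the information this discards. The article does not support that: it ties the logistic model to no outcome, sets no cut-point and mentions no median split.

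It is also too strong to say that no logistic model could be used. An ordinal logistic model can be fitted to ranked days, and the alleviation of feeding intolerance described in section 3.10.2 could be coded yes or no. The article says neither is intended. The fair statement is that no adjusted model suited to the primary outcome is named.

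A reader might further infer that leaving out the strata invalidates the test, or always makes it conservative. Neither follows. The type I error is not inflated, and conservatism needs within-stratum balance. Nor does the omission cause a shortfall against the planned sample size, which was worked out without strata; what is forgone is a gain.

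Finally, covariates and model details are commonly left to an analysis plan. That would answer silence, but the article is not silent: it names one model and a set of unstratified tests.

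**Conclusion.** The point holds as a mismatch between the stated methods and the outcomes and design. That part rests on the text alone and is firm. The unadjusted comparison is valid, so this is a matter of precision and clear specification and does not threaten the trial's conclusion.

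The size is much less certain. Under the stated assumptions, including the back-calculated SDs, the power forgone is about 4 to 13 points at SD 9.49 (73 − 69 and 82 − 69) and about 5 to 10 points at SD 7.26 (94 − 89 and 99 − 89). It is somewhat smaller if arms are balanced within strata, because the unadjusted test then has a little more power. If birth weight hardly predicts time to full feeds, the gain is close to nil. The change should be made because it costs almost nothing, even though the loss cannot be fixed to one figure.

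**What to change.** In section 3.12 and in any analysis plan:

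- Make the primary analysis of days to full enteral nutrition a linear regression with treatment and birth-weight stratum, reporting the adjusted difference with its 95% interval. If a rank test is kept, use the stratified (van Elteren) form. State now which of the two is primary.
- Use linear regression with treatment and stratum for the other continuous outcomes.
- Keep logistic regression only for outcomes that are truly binary, and name them.
- Name any further covariates in advance.
- State whether allocation was blocked within strata, so that readers can judge how the unadjusted test behaves.

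The cost is wording. The stratum is known for every randomised infant, because the envelope was drawn from that stratum's set, so no new data are needed. Recruitment was still open when the article was submitted (section 3.14) and analysis follows completion of data collection (section 3.12), so the change can be made before any result is seen. If the rank test is chosen, check that the planned software provides the stratified form.

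### The primary hypothesis and effect measure are left to the observed distribution, although the trial is sized on a difference of two means

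*Protocol article*

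**What the plan says.** All references are to the protocol article.

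- **Primary outcome (3.10.1):** "The time (day) from initiation of enteral nutrition to total enteral nutrition", so a continuous outcome in days.
- **Sample size calculation (3.4):** "This study is a superiority test of two independent means", with expected means of 28.3 and 33.5 days, 41 infants per group, and 52 per group after a 20% loss rate.
- **Statistical analysis (3.12), first branch:** "Measurement data obeying the normal distribution will be expressed as mean (standard deviation", with a t-test between groups.
- **Statistical analysis (3.12), second branch:** "Non‐normally distributed variables will be expressed as median (interquartile range", with the Wilcoxon-Mann-Whitney test between groups.
- **Same section, missing data:** "Missing data will be forecasted and filled using multiple imputations".
- **Same section, adjustment:** the only model named for confounders is logistic regression.
- **Randomization and blinding (3.6):** a third party "created a randomization schedule which was stratified by birth weight", in two strata, 1000-1499 g and 1500-2000 g.

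Section 3.12 makes no exception for the primary outcome, so the distribution rule governs it.

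**The concern.** The two branches answer different questions. The t-test compares mean days, which is what the sample size was built on. Mann-Whitney asks whether infants in one arm tend to reach full feeding sooner than infants in the other, and medians with quartiles describe each arm without giving a difference in mean days. If the second branch is taken, the trial's main conclusion no longer addresses the planned 5.2-day difference. Which question is asked is known only after the outcome data are seen.

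Two further parts of the plan sit badly with the rule. Multiple imputation produces several completed data sets, and normality may be accepted in some and rejected in others, so the rule names no single quantity to combine. And the randomisation is stratified by birth weight, but neither test uses the strata, while a logistic model does not suit an outcome measured in days.

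**Working it through.** **1. The plan's own figures.** Loss adjustment: 41 / (1 - 0.20) = 51.25, rounded up to 52 per group, 104 in total. This reproduces. The 41 itself cannot be confirmed, because section 3.4 gives no number for the SD.

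**2. SD implied by 41 per group.** For two means with equal groups, n = 2(Zα + Zβ)²σ²/δ², so σ = δ√(n/2)/(Zα + Zβ), with δ = 33.5 - 28.3 = 5.2 days. At n = 41, δ√(n/2) = 5.2 × √20.5 = 23.54.

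- One-sided 0.025, power 0.90: 23.54 / (1.960 + 1.282) = 7.26 days.
- The printed Z values: 23.54 / (1.64 + 0.84) = 9.49 days.
- Two-sided 0.025, power 0.90: 23.54 / (2.241 + 1.282) = 6.68 days.

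The printed Z values do not match the stated α and power. That is a separate matter; here it only sets a range. I used 7.26 and 9.49 days.

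**3. The rule in simulation.** Assumptions not in the article: 41 per arm, normal or log-normal data, t-test if Shapiro-Wilk p > 0.05 in both arms and Mann-Whitney otherwise, two-sided 0.05, and 5,000 trials per row. Null rows have mean 33.5 in both arms; planned rows have 28.3 versus 33.5.

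| Scenario | SD | Rule picks Mann-Whitney | t-test significant | Mann-Whitney significant | Rule significant | Tests disagree |
|---|---|---|---|---|---|---|
| Null, normal | 7.26 | 10.4% | 4.7% | 4.4% | 4.6% | 2.1% |
| Null, log-normal | 7.26 | 49.3% | 5.4% | 5.1% | 5.6% | 2.3% |
| Null, normal | 9.49 | 9.9% | 4.8% | 4.5% | 4.9% | 2.1% |
| Null, log-normal | 9.49 | 68.5% | 4.6% | 4.6% | 5.0% | 2.6% |
| Planned, normal | 7.26 | 9.7% | 89.7% | 88.9% | 89.6% | 3.2% |
| Planned, log-normal | 7.26 | 54.4% | 89.5% | 91.0% | 91.2% | 4.4% |
| Planned, normal | 9.49 | 10.4% | 68.6% | 66.3% | 68.5% | 6.6% |
| Planned, log-normal | 9.49 | 74.2% | 69.0% | 74.5% | 74.6% | 9.9% |

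Hand check on the normal rows: two independent 5% checks both pass with probability 0.95², so the rule leaves the t-test in 1 - 0.9025 = 9.75% of trials.

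**4. Do the branches test the same thing?** With equal means of 33.5 days but log-normal SDs of 5 and 15, the t-test rejects in 5.5% of trials, Mann-Whitney in 20.5% and the rule in 19.8%. Nothing in the article suggests such spreads. The case only shows that the hypotheses differ.

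**5. Imputation.** With 52 per arm, log-normal data at the planned means, 20 imputations from a normal model within arm and 300 trials per cell, the share of trials in which the normality verdict differs among the 20 data sets is:

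| Outcomes imputed | SD 7.26 | SD 9.49 |
|---|---|---|
| 5% | 46% | 33% |
| 10% | 51% | 44% |
| 20% | 72% | 64% |

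The simulation error is about ±3 points (√(0.5 × 0.5/300) = 0.029), and another imputation model would give other rates.

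**6. Can the rank result be pooled at all?** Yes, if an estimate is defined. Taking the probability that a massage infant reaches full feeding before a control infant, with its variance, and applying Rubin's rules over 20 imputations (20% imputed on the log scale, SD 9.49, 1,000 trials) gave 5.7% rejection under the null and 76% under the planned difference. Section 3.12 defines no such estimate.

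**The case against.** The best defence is that the rule is conventional and does little harm to error rates. That stands in part: applied mechanically, with both arms sharing one distribution, it rejects in 4.6-5.6% of null trials. A reader might infer a raised false-positive risk, but the article ties the choice to the distribution and not to the result, so inflation would need an analyst to depart from the text by reporting whichever test is favourable.

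Three other strong readings also fail.

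- **That a rank result cannot be pooled over imputations.** Step 6 shows that it can. What is missing is a defined estimate and standard error; medians and rank p-values have no direct pooling without them.
- **That two analysts would reach different verdicts in 3-10% of trials.** That figure is how often the two tests disagree. Two analysts would differ only if their normality judgements differed and the tests also disagreed, and that rate was not computed.
- **That ignoring the strata costs a known number of infants.** The article gives no figure for how much of the variance birth weight explains.

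It is also fair to say that few primary values may need imputing. The outcome is recorded in hospital, death or discharge before total enteral nutrition is an exit criterion (Table 1), and section 3.11 removes infants who discontinue or deviate.

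Finally, a condensed article may leave the normality criterion and the pooling rule to a fuller document. That does not answer the main point, which is a rule the article states and which does not match the hypothesis it was sized on.

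**Conclusion.** The point holds as a defect in what is fixed in advance. The article commits to a mean difference for sample size and then lets the data replace it with a different hypothesis that has no stated effect measure. Under the assumptions of step 3, the replacement is occasional if days to full feeding are normal and roughly as likely as not, or more likely, if they are log-normal.

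The conflict with multiple imputation is real in principle, but its practical size depends on how many primary outcomes are imputed, which the article does not say. The unused strata and the unsuitable logistic model strengthen the case for naming one model, without a size attached. The numbers rest on an assumed SD, shape and normality check; the implied SD of about 6.7 days under the two-sided reading of α lies below the range simulated. The plan should be changed, but the finding does not make a result obtained under the rule invalid.

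**What to change.** For the primary outcome, replace the distribution-dependent choice with one prespecified analysis: a linear regression of days to total enteral nutrition on arm and birth-weight stratum, with robust standard errors. Report the adjusted mean difference with its 95% CI, combined by Rubin's rules where outcomes are imputed. Keep Mann-Whitney as a sensitivity analysis. A Cox model would not serve this purpose, since a hazard ratio gives no difference in mean days either.

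The cost is a short change of wording, with no extra data or infants, and recruitment was still open when the article was submitted. Because the target remains the mean difference, 41/52/104 stays as planned. By contrast, fixing Mann-Whitney as primary would, with normal data (efficiency 0.955), need 41/0.955 = 42.9, so 43 per group; 43/0.80 = 53.75, so 54 per group and 108 in total.

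The downside is some power if the data are strongly skewed. In the log-normal rows, the t-test trails Mann-Whitney by 91.0 - 89.5 = 1.5 points at SD 7.26 and by 74.5 - 69.0 = 5.5 points at SD 9.49.

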### Participants: Inclusion/exclusion criteria

3.3

Table 1 specifies the criteria for inclusion, exclusion, termination and exit criteria. Inclusion and exclusion criteria were defined according to previous literature (Baldassarre et al., 2019; Ng et al., 2018; Yakobson et al., 2020).

**TABLE 1 nop21733-tbl-0001:** Inclusion, exclusion, termination and exit criteria.

*Inclusion criteria*
Meet the FI diagnostic criteria
Admitted to the Neonatal Treatment Center of the Affiliated Children's Hospital of Chongqing Medical University within 24 h after birth
28 weeks ≤ gestational age ≤ 34 weeks, 1000 g ≤ birth weight ≤ 2000 g
In clinically stable condition
The neonate's guardians are willing to participate in this trial
*Exclusion criteria*
Apgar score less than 4 at 5 min
Neonates with skin disease, intestinal obstruction, sepsis, necrotizing enterocolitis, gastrointestinal malformation, congenital heart disease, central nervous system disorder, immune deficiency, or any other disease that may affect the ability to eat and normal growth before recruitment
Neonates who need surgery which requires general anaesthesia (except for ligation of patent ductus arteriosus) before the day of randomization
Neonates whose blood pressure is not stable (using dopamine <5 mg /kg/min is permitted)
Ventilator dependent or FiO_2_ (Fraction of inspired oxygen) > 40% on the day of randomization (continuous positive airway pressure, nasal intubation, oxygen mask are allowed)
Neonates who are diagnosed with Grade III or IV ventricular haemorrhage (IVH) on the day or before randomization
*Termination criteria*
Discharge in a stable condition with doctor's advice
*Exit criteria*
Death or discharge before achieving total enteral nutrition
Guardian request to withdraw from the trail

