### Variables studied

3.7

A researcher who has no access to the allocation group will perform all the assessments for our study. Table 2 shows the demographic variables including maternal characteristics and neonatal characteristics of participants recruited in our trial.

**TABLE 2 nop21733-tbl-0002:** Demographic variables.

Variables	Values
*Maternal characteristics*	
Caesarean delivery	Yes/no
Twin pregnancy	Yes/no
Gestational hypertension	Yes/no
Diabetes during pregnancy	Yes/no
Intrauterine distress	Yes/no
*Neonatal characteristics*	
Gestational age	Weeks
Day of recruitment	Day
Birth weight	g
Boy	Yes/no
Apgar score at 5 min	1–10
Weight at recruitment	g
neonatal critical illness score	Yes/no
Routine treatment received	Antibiotics/caffeine citrate/type of feeding

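### Both members of a twin pair may be enrolled, yet every named test treats infants as independent and omits the birth-weight stratum; the cost is modest and cheap to avoid

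*Protocol article*

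**What the plan says.** Section 3.7, Table 2 of the protocol article lists "Twin pregnancy" (yes/no) among the maternal baseline variables, so twins are expected. The eligibility limits in section 3.3, Table 1 are "28 weeks ≤ gestational age ≤ 34 weeks, 1000 g ≤ birth weight ≤ 2000 g", with further clinical conditions; no criterion excludes multiples or restricts a family to one infant.

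Section 3.6 allocates infant by infant within birth-weight strata: "Participants were assigned randomly to one of the two groups by opening the next envelope sequentially from the appropriate set". It gives no rule for siblings.

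Section 3.4 sizes the trial on the same footing: "This study is a superiority test of two independent means". In section 3.12 the sentence beginning "Measurement data obeying the normal distribution will be expressed as mean (standard deviation" goes on to name the t-test. The Wilcoxon-Mann-Whitney test is named for non-normal data, the chi-square test for categorical data, and a logistic model for confounders. No section mentions pairs, a family effect or robust standard errors, and section 3.12 does not bring the stratification factor into the comparison of arms.

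**The concern.** Co-twins share a mother and, almost always, a gestational age. The requirement of admission within 24 hours of birth puts them on the ward at the same time. Their times to full enteral nutrition, lengths of stay and growth are therefore likely to be correlated.

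A two-sample test on infants ignores that correlation. When the two members of a pair go to different arms, their shared component cancels in the difference, and the t-test's standard error is too large. When both go to the same arm, the shared component adds up, and the standard error is too small. The trial reports one interval from one realised allocation, and the named tests cannot show which case applies. They also discard the within-pair contrast, which costs no extra infants to use. Leaving out the birth-weight stratum discards further precision if birth weight predicts the outcome.

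**Working it through.** **Inputs from section 3.4.** Means of "28.3 days and 33.5 days respectively", a difference of 33.5 − 28.3 = 5.2 days; "desired power was set at 0.9"; alpha "was set at 0.025"; 41 per group before loss; 20% loss. Section 3.12 tests at 0.05.

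**Inputs not in the documents, so assumed.** The number of complete pairs m among 104 infants, and the within-pair correlation rho. Central case: m = 13 (26 infants, 25% of 104) and rho = 0.5. Range: m = 8 to 21 and rho = 0.3 to 0.7.

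**1. The plan's own figure.** 41/(1 − 0.2) = 51.25, rounded up to 52 per group and 104 in total; this reproduces. The 41 cannot be checked because no standard deviation is given. With one-sided 0.025 and power 0.90 it needs an SD of about 7.17 to 7.26. How the quantiles printed in section 3.4 fit the stated alpha and power is a separate matter.

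**2. Error averaged over allocations.** The plain t-test was simulated under individual 1:1 allocation of 82 infants.
- 12 pairs, rho 0.5: type I error 0.050.
- 16 pairs, rho 0.7: type I error 0.049.
- 12 pairs, rho 0.5, difference 5.2 and assumed SD 7.2: power 0.897.

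The expected design effect is therefore about 1, and twins give no reason to enlarge the trial.

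**3. Error for the realised split.** With n = 52 per arm, C pairs together and D pairs split:

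variance ratio (true ÷ assumed by the t-test) = 1 + rho × (C − D)/52

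type I error = 2 × [1 − Φ(1.96/√ratio)]

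If each pair is equally likely to be together or split, C − D has mean 0 and SD √m. For m = 13, √13 = 3.61, so ±2 SD is ±7.21.

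| Split (m = 13, rho = 0.5) | Variance ratio | Type I error |
|---|---|---|
| −2 SD | 1 − 0.5 × 7.21/52 = 0.931 | 4.2% |
| +2 SD | 1 + 0.5 × 7.21/52 = 1.069 | 5.8% |
| All 13 split (bound) | 1 − 0.5 × 13/52 = 0.875 | 3.6% |
| All 13 together (bound) | 1 + 0.5 × 13/52 = 1.125 | 6.5% |

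Each bound has probability 2^−13, about 1 in 8,000. At the most adverse assumption (m = 21, rho = 0.7), ±2 SD is ±9.17, the ratio is 1 ± 0.123, and type I error is 3.6% to 6.4%. With 5 pairs and rho 0.5 it is 4.5% to 5.5%.

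**4. Precision lost.** With half the pairs together and half split, information per paired infant in a model that uses the pairing averages

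0.5/(1 + rho) + 0.5/(1 − rho) = 1/(1 − rho²)

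The overall gain is (2m/104) × [1/(1 − rho²) − 1].
- m = 13, rho = 0.5: 0.25 × 0.333 = 8.3%. The model would then need 104/1.083 = 96 infants to match the t-test on 104, a saving of 8.
- m = 8, rho = 0.3: 0.154 × 0.099 = 1.5%.
- m = 21, rho = 0.7: 0.404 × 0.961 = 38.8%.

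**The case against.** The strongest reply is that there is no validity problem: type I error is nominal on average, power is not reduced, and a typical split moves the error rate by less than one percentage point in the central case. That is right and sets the scale of the point.

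Co-enrolment is also inferred rather than stated. A complete pair needs both infants to have feeding intolerance, meet every criterion in Table 1 and have consent. Both must then stay in the analysis, although section 3.11 drops infants who discontinue or deviate. Few or no complete pairs is compatible with the text, and the effect then nearly vanishes. This stands too.

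It can further be said that correlation structure belongs in a full analysis plan that is not shown. This carries less weight. Section 3.12 names the tests and section 3.4 states independence, so the published choice does not fit data the trial may hold. That is more than an unstated detail.

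A reader might go further and infer that the pairs cannot be linked, because Table 2 records twin status only as yes or no. The documents do not support that: in section 3.11, Table 3, CRF1 also holds contact information and maternal issues, from which siblings could plausibly be matched.

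Finally, a linear model alone would not answer the plan's provision for non-normal data. That is a fair criticism of a bare mixed-model remedy, and the change proposed here has to deal with it.

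**Conclusion.** The point holds as a modest mismatch between the named analysis and the data the trial may contain. Assuming 13 complete pairs and a correlation of 0.5, the type I error for the realised split is about 4.2% to 5.8% in typical cases, and about 8% of information is forgone (1.5% to 38.8% over the assumed range, near zero if few complete pairs are enrolled). Both assumed inputs lie outside the documents.

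Two stronger readings are tempting and fail. One is that 104 is too small or needs a design effect: under individual randomisation the average design effect is about 1. The other is that the error rate is inflated to 6.5%, or to 8.4% with 21 pairs and a correlation of 0.7: those values need every pair to fall in the same arm as its co-twin, which has negligible probability, and the error is as likely to be conservative.

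The averaging assumes that a pair is about equally likely to be together or split. If the schedule uses small blocks, which the article does not say, co-twins drawing consecutive envelopes would be split somewhat more often, which makes the t-test slightly conservative.

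**What to change.** - **Family identifier.** Record one, or derive it from the contact and maternal data already on CRF1.
- **Primary outcome.** Before unblinding, specify in section 3.12 a linear mixed model with a random intercept for mother, or GEE with exchangeable correlation and robust standard errors. Enter arm and birth-weight stratum as fixed effects.
- **Skewed data.** State in advance that, if time to full feeds is skewed, a log scale or the GEE with robust standard errors replaces the plain Wilcoxon-Mann-Whitney test. On a log scale the effect is a ratio, and the text should say so.
- **Other outcomes.** Use the same structure for length of stay and growth.
- **Unchanged.** Keep individual randomisation and the sample size.

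The cost is one data field, a sentence or two of analysis text and slightly more work in SPSS 25; no extra infants are needed. The drawback is that the within-pair correlation will be estimated imprecisely from few pairs, so the realised gain may fall short of the calculated one. The article reports recruitment as still incomplete at submission. If unblinding has not yet occurred, the change can still be made without knowledge of results.
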